#### Analysis

We will first conduct descriptive statistical analysis of baseline variables and clinical characteristics of the two intervention arms to examine the extent, if any, of baseline or clinical imbalances between the two arms using contingency table analyses (Mantel-Haenszel for categorical and analysis of variance for continuous variables). The analysis will center around estimating the impact of the intervention on each of the primary study outcomes, observed at baseline and 6- and 12-month follow-up visits, using all available cases consistent with an intent-to-treat method. In addition to evaluating changes in each outcome by intervention arm at 6-month follow-up, the analysis will examine whether the changes are sustained or decay at 12-month follow-up. Given the longitudinal nature of the data, our primary analytic strategy will apply a generalized estimating equation (GEE) modeling approach to account for the multiple dependencies of repeated measures collected on the same individuals over time, and the clustering of the outcomes by community. Because the communities may range from 5 to 100 cases, the generalized linear/nonlinear mixed model (e.g., hierarchical linear modeling or multilevel modeling with random effects) would likely face problems with convergence given the heterogeneity in the variation between communities. Therefore, we opt for a statistical strategy that treats this level of clustering as a nuisance parameter, and thereby estimating the population-averaged effects of the outcomes for subjects sharing the same profile of individual and community-level characteristics. For outcomes with binomial or count distributions, the logit link will be specified to obtain effect estimates of the magnitude of differences between arms within each follow-up visit. For continuously distributed outcomes, an identity link function will be specified. We expect that we will estimate the working correlation matrix at the temporal level using a first-order autoregressive structure (AR-1) and an exchangeable correlation matrix at the community-level, thereby allowing the subjects within each cluster to be constrained to equality but freeing the estimates between clusters.

In addition to the main outcome analyses, we will examine the mechanism of change via standard mediational models. For this approach, we will lag the timepoints such that the baseline will be the most exogenous, then the midpoint 6-month observation will be the mediator and the 12-month observation will serve as the distal outcome. We can also estimate a mediational model with two timepoints, estimating the distal outcome at 6 months along with the concurrent mediator. These models will be fit using standard structural equation modeling software packages (e.g., Mplus), which can adjust the standard errors via bootstrapping to reduce bias and also remove exogenous measurement error. These models can be estimated using a mixture of distributions, such as a categorical mediator or outcome in concert with a continuously distributed mediator or outcome. The mediational analyses will address the extent to which the intervention worked and estimate the direct and indirect mechanisms. However, moderational analyses will address the extent to which the intervention worked for specific subgroups, such as women who are HIV positive, women in a relationship, and women with a criminal history. For these analyses, interaction terms will be created by multiplying the effect of the intervention by the moderator variable of interest.

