### Randomization

We created seven pairs of zones that were matched on the basis of socioeconomic conditions and estimates of the number of sex workers and women who use AOD residing in them. These estimates were based on inputs from our outreach workers who had worked on one of our prior studies that reached drug-using, at-risk women and sex workers in the Pretoria area [23–25].

We randomized zones within each pair to the control arm or the intervention arm. Each participant’s study arm is determined by the zone in which she was recruited.

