#### Sample size and power

The sample size was lowered to 600 from 1050 as originally planned. The original sample size was calculated on the basis of an anticipated HIV prevalence of 30%; however, HIV prevalence in the sample is 55%. Accordingly, the smaller sample (n = 600) will allow for the identification of a clinically meaningful effect with sufficient statistical power, while accounting for logistical difficulties, including a citywide study, limited structural resources, increased costs, and other factors outside the control of the study. We assume 14 clusters, approximately 30 observations per cluster and 20% attrition, yielding a final sample size of about 480 respondents at 12-month follow-up. This allows us a medium to strong likelihood of detecting an effect of the intervention assuming a strong effect (based on Cohen’s beta of 0.6). This would translate to an approximately 10% to 15% difference in the outcomes for any behavioral outcome (e.g., reductions in AOD use, number of instances of unprotected sex). We would not be able to detect mild to weak effects in analyses that consider the mediation of the effect of the intervention through some cognitive outcome, such as intentions/self-efficacy/knowledge/gender power. The reduction in power also greatly reduces the likelihood of testing whether the intervention yielded modification effects across the levels of some covariate and mediational effects as well. However, we will examine the distribution of the variables and reestimate power given the final sample size and variance estimates. No outcome or mediator/moderator analyses will be conducted unless there is strong power (e.g., Beta greater than .8, for a 2-tailed test and p = .05).

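### Baseline imbalance between arms is to be tested with woman-level Mantel-Haenszel and ANOVA although zones were randomized, so the p-values will be too small (minor)

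*Protocol article*

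**What the plan says.** The Randomization section of the protocol article fixes the unit of allocation. It says "We created seven pairs of zones that were matched on the basis of socioeconomic conditions" and on estimated numbers of sex workers and women using alcohol or drugs. It continues: "We randomized zones within each pair to the control arm or the intervention arm". A participant's "study arm is determined by the zone in which she was recruited".

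The Analysis section opens with a descriptive comparison of the arms at baseline, meant "to examine the extent, if any, of baseline or clinical imbalances between the two arms". The tools it names are "contingency table analyses (Mantel-Haenszel for categorical and analysis of variance for continuous variables". It sets no significance level for this step, states no action that would follow from a finding, and does not mention zone. Clustering enters only afterwards, in the GEE outcome model, which is to allow for repeated measures and for "the clustering of the outcomes by community".

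**The concern.** Mantel-Haenszel and analysis of variance, applied to women, judge an arm difference against the variation expected if the women were independent. Here chance worked on zones. Women from one zone share its circumstances, and the Setting section describes zones as different as commercial districts and informal settlements. An arm contrast therefore carries the chance variation of seven zones against seven, and a woman-level test leaves that variation out of its standard error.

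What is at stake is how the baseline table is read. Outreach workers recruit in zones whose arm is already fixed, so a reader will look to the baseline comparison for signs of selective recruitment. P-values that react to ordinary zone differences cannot separate those from a real recruitment difference.

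**Working it through.** **Inputs from the article.** There are 14 zones in 7 pairs (Randomization). The sample is 600 women: "The sample size was lowered to 600 from 1050 as originally planned". Zone sizes may run from 5 to 100 (Analysis; I take its communities to be the zones). A two-sided 5% level appears under Sample size and power, but for the outcome, mediator and moderator analyses. I borrow it for the baseline tests as an assumption.

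**Inputs assumed.** The article gives no ICC, so I show 0.01 and 0.05. The gain from matching is also unknown, so I show none and half of the between-zone variance.

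**The plan's own figure.** The article gives no error rate for the baseline tests. The nearest figure is the sample size: "We assume 14 clusters, approximately 30 observations per cluster and 20% attrition, yielding a final sample size of about 480 respondents at 12-month follow-up". 600 × 0.80 = 480 reproduces it; 14 × 30 = 420 does not. For baseline the relevant mean zone size is m = 600/14 = 42.9, and I use 30 as a sensitivity value.

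**Formula, equal zones, no gain from matching.** The variance of the arm difference is inflated by DE = 1 + (m − 1) × ICC. A nominal 5% test that ignores zone then rejects with probability 2 × [1 − Φ(1.96/√DE)].

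- ICC 0.01: DE = 1 + 41.9 × 0.01 = 1.42; 1.96/√1.42 = 1.65; rejection 10.0%.
- ICC 0.05: DE = 1 + 41.9 × 0.05 = 3.09; 1.96/√3.09 = 1.11; rejection 26.5%.
- With m = 30 the rates are 8.4% and 21.1%.

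**Formula, matching removes half of the between-zone variance.** The inflation becomes 1 + (m/2 − 1) × ICC.

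- ICC 0.01: 1 + 20.4 × 0.01 = 1.20; rejection 7.4%.
- ICC 0.05: 1 + 20.4 × 0.05 = 2.02; rejection 16.8%.

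**Simulation.** I ran 20,000 trials per setting with a binary baseline variable of prevalence 0.5, no arm imbalance beyond chance, and zones randomized within 7 pairs. Zones were either all of size 43 or an assumed set from 5 to 100 totalling 600. Rejection at nominal 5%:

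| Zones, gain from matching | Test | ICC 0.01 | ICC 0.05 |
|---|---|---|---|
| Equal, none | pooled, on women | 9.6% | 25.8% |
| Equal, none | Mantel-Haenszel by pair | 10.0% | 26.8% |
| 5 to 100, none | pooled, on women | 12.1% | 33.1% |
| 5 to 100, none | Mantel-Haenszel by pair | 12.0% | 33.3% |
| Equal, half | pooled, on women | 7.4% | 16.8% |
| 5 to 100, half | pooled, on women | 8.9% | 21.4% |

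A second set of unequal zones, from 5 to 105, gave 12% and 34% for a binary variable and the same for a continuous one. At ICC 0 the pooled test rejected in 4.6% to 5.3% of trials, as it should.

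Two things follow. Stratifying Mantel-Haenszel by pair does not cure the problem. A paired t-test on the seven differences in zone proportions (6 degrees of freedom) rejected in 4.8% to 5.2% of trials with equal zones and 3.6% to 4.9% with unequal zones, so the excess comes from the unit of analysis.

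**The case against.** The strongest reply is that this is a descriptive table. No significance level is attached to it, no covariate is selected from it, and the outcome model is designed to allow for clustering. All of that stands, and it limits the consequence. It does not make the named tests fit the design.

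A second reply is that a journal article is condensed, and that a fuller plan may put zone into the ANOVA or use a cluster-adjusted version. That is possible, and that women are to be treated as independent is an inference from the tests named. But the article names particular tests for a particular purpose and mentions clustering only for outcomes, so the text as it stands needs correcting.

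A third reply is that matching could remove much of the zone variation. It may, since the matching factors plausibly relate to many baseline variables. Even if half of that variation goes, rejection stays above 5% at both ICCs.

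Three stronger readings are tempting:

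- A reader might infer a fixed multiple of the nominal rate. The article supplies neither the ICC nor the threshold that this would need. Over ICC 0.005 to 0.10, with and without the matching gain, the simulated rates ran from 5.9% to 47.4%.
- A reader might infer that the extent of imbalance will be overstated. Ignoring zone shrinks p-values; it does not inflate the observed difference in means or percentages.
- A reader might infer that false alarms will drive adjustment of the outcome model. Nothing in the Analysis section links the two.

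**Conclusion.** The concern holds as a minor point. Unless zones vary no more than sampling of women would produce, the stated baseline tests give p-values that are too small for a trial that allocated zones. The rates of about 10% to 12% (ICC 0.01) and 26% to 34% (ICC 0.05) without a matching gain, and 7% to 9% and 17% to 21% with half the between-zone variance removed, are conditional illustrations. They rest on an assumed ICC, a borrowed 5% level and, for the upper ends, an assumed spread of zone sizes.

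The error lies in statistical significance only. The observed arm differences are unbiased descriptions of the enrolled sample, and the estimate, standard error and type I error of the primary GEE analysis do not depend on these tests.

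**What to change.** Replace the sentence that names Mantel-Haenszel and analysis of variance. Report baseline summaries by arm with standardized differences, and without woman-level significance tests.

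If a test is wanted to detect selective recruitment, make it a zone-level one that respects the pairs. One choice is a paired comparison of zone summaries. The other is a permutation of the allocation within the seven pairs, which has 2^7 = 128 allocations and a smallest two-sided p of 2/128 = 0.016.

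The cost is one sentence in the plan and a little programming. The downside is that seven pairs give low power for small imbalances, so a non-significant result should not be read as evidence of balance.

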#### Intervention arm

Women in the intervention arm participate in all of the activities described above for the control arm. In addition, they participate in two individual, woman-focused HIV prevention intervention sessions. These sessions aim to increase knowledge, skills, and motivation to make behavioral changes related to AOD use, sexual risk, and violence and victimization. These sessions take place at the field site and are facilitated by an experienced female interventionist who is a multilingual peer leader from the community and who also is sensitive to helping women develop empowerment strategies with a personalized plan after the intervention session.

The WHC is an evidence-based, woman-focused, behavioral intervention that reaches high-risk, hard-to-reach, vulnerable women. It addresses the intersecting risks of drug use, sex behaviors, violence and victimization, with the primary goal of increasing skills and knowledge. The WHC has been adapted from previous iterations in North Carolina, Rhode Island, Massachusetts, Russia, the Republic of Georgia, and South Africa. It is based on social cognitive theory and empowerment theory [29]. Two intervention sessions are held approximately 3 to 5 days apart. Each session lasts 30 to 45 minutes. Key elements of the sessions educate participants about the risks of AOD use and how AOD use and sex risk relate to HIV for women. The sessions also teach risk-reduction methods such as proper condom use, sexual negotiation, and violence prevention strategies. Women also role-play and rehearse how to use male and female condoms correctly, as well as condom negotiation. During the sessions, the women create personalized action plans in which they develop a concrete plan to reduce risk. At the end of the second session, the participant completes the personalized plan, which she takes home as a guideline for her set goals. The staff conducts case management face to face or by cell phone at least monthly to follow up and support the participant in her risk-reduction and action plan to improve her life. For women with AOD use problems, the interventionists work closely with drug rehabilitation facilities to secure treatment slots.

Because this adaptation of the WHC combines TTR activities with a specific focus on linking women to care if they are newly or previously diagnosed with HIV before enrollment, we named this combined biobehavioral intervention the Women’s Health CoOp Plus (WHC+).

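### Available-case GEE is presented as intent-to-treat, but with 20% planned attrition it gives that comparison only if loss is unrelated to condom use given what the model uses

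*Protocol article*

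**What the plan says.** All references are to the protocol article.

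- **Analysis** fixes the primary method: "our primary analytic strategy will apply a generalized estimating equation (GEE) modeling approach". The outcomes at baseline, 6 and 12 months are to be analysed "using all available cases consistent with an intent-to-treat method". The expected working correlation is described as "using a first-order autoregressive structure (AR-1) and an exchangeable correlation matrix at the community-level".
- **Sample size and power** plans for "20% attrition, yielding a final sample size of about 480 respondents at 12-month follow-up". The 20% is a single overall figure and is not split by arm. The same section puts the detectable difference at about 10% to 15%.
- **Outcome measures** makes the primary outcome self-reported condom use at the most recent intercourse, so it is known only if the woman is interviewed.
- **Intervention arm** adds two sessions and continuing contact to everything that controls receive: "The staff conducts case management face to face or by cell phone at least monthly". **Control arm** describes no comparable contact between follow-up visits.
- Tracing with locator information (Ethical approval), follow-up incentives (Changes in incentives), field follow-up interviews (Miscellaneous changes) and transport, meals and childcare (Control arm) are not described as differing by arm.

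**The concern.** The Analysis section treats using every observed visit as if that secured an intention-to-treat comparison. Keeping women in the arm of their recruitment zone is one part of such a comparison. The other part is dealing with the one woman in five who was randomised but has no 12-month outcome. Unweighted GEE leaves her 12-month outcome out, and this is harmless only under a condition that the section does not state.

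The design makes a breach of that condition plausible. Regular contact in one arm may hold on to women whom the other arm loses. The traits that make a woman hard to find, such as sex work, heavier alcohol or drug use and unstable lodging, may also go with lower condom use. If controls lose more such women, the controls who remain look safer than the randomised control group and a real effect is understated. If the extra contact retains a selected group instead, the bias can run the other way.

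**Working it through.** **1. The plan's own figure.** 600 × (1 − 0.20) = 480, which matches the stated number at 12 months. (14 clusters × 30 = 420, which matches neither 600 nor 480. That is a separate matter and is not used here.)

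**2. Bias among women seen at 12 months.** Let an arm have true proportion μ, attrition a, and a gap g in condom use between retained and lost women. Since μ = (1 − a) × retained + a × lost, the retained proportion is μ + a × g. With the same gap in both arms,

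bias in the difference = (a_intervention − a_control) × g.

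The document gives only the overall 20%. The splits 12/28 and 16/24 are assumptions that average 20% with arms of equal size. The gaps are assumptions too.

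- 12/28, g = 20 points, true effect 10 points: control 0.50 + 0.28 × 0.20 = 0.556; intervention 0.60 + 0.12 × 0.20 = 0.624; difference 0.068, a shortfall of 3.2 points.
- 16/24, g = 10 to 30 points: 0.08 × 0.10 = 0.008 to 0.08 × 0.30 = 0.024, a shortfall of 0.8 to 2.4 points.
- g = 0: no bias, whatever the split.

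**3. Loss that depends on condom use itself, with no true effect.** Suppose condom use is 50% in both arms, attrition is 15/25, and non-users are twice as likely to be lost.

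- Intervention: loss among users 0.15 / (0.5 + 0.5 × 2) = 0.10; observed use 0.5 × 0.90 / 0.85 = 0.529.
- Control: loss among users 0.25 / 1.5 = 0.167; observed use 0.5 × 0.833 / 0.75 = 0.556.
- Spurious difference: −2.6 points.

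With equal attrition of 20/20 and the same mechanism in both arms, the difference is 0.0.

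**4. Longitudinal GEE.** Steps 2 and 3 use only the 12-month visit. The planned model also uses earlier visits, so simulation is needed. These runs have three visits and, in those whose design is recorded, no zone clustering.

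| Driver of loss | Attrition, intervention/control | Working correlation | Bias (points) |
|---|---|---|---|
| Arm only | 15/25 | independence; exchangeable | +0.7 (within Monte Carlo error); 0.0 |
| 6-month outcome, controls only | 15/25 | independence; exchangeable | −2.4; −0.1 |
| Arm only | 15/25 or 12/28 | AR-1 | 0 |
| 6-month outcome | 15/25 or 12/28 | AR-1 | about 0 |
| Baseline trait outside the model, loss at 12 months only | 15/25 or 12/28 | AR-1 | −0.3 to −0.5 |
| Baseline trait outside the model, loss at 6 and 12 months | 12/28 or 16/24 | AR-1 | 0.6 to 3.8 in size |
| Unobserved current condom use | 15/25 or 12/28 | AR-1 | −2.2 to −3.6 |

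In the sixth row, imputation using the trait and prior outcomes removed the bias. In the same set of runs, loss driven by unseen condom use left 1 to 2 points, which imputation and weighting on observed predictors are not built to remove.

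**5. Reading the range.** By the formula in step 2, 0.6 points at 16/24 corresponds to a gap of 0.6 / 0.08 = 7.5 points, and 4 points at 12/28 to 4 / 0.16 = 25 points. The upper end therefore needs a strong link between loss and condom use. Against the target, 0.6 / 15 = 4% and 4 / 10 = 40% of the effect sought.

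**6. No-assumption bounds.** The unseen outcomes allow a range as wide as the two attrition rates added together: 0.12 + 0.28 = 0.40, or 0.16 + 0.24 = 0.40. That is 40 points, against a target of 10 to 15.

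**The case against.** The strongest reply has four parts.

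*Missing-data detail belongs in an analysis plan that is not shown, and the phrase may mean only that women are analysed in the arm of their zone.* Silence on imputation would indeed be no finding. But the article does not only stay silent: it names the primary analysis set and method and says that this agrees with intention to treat. That statement can be judged as it stands.

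*GEE does not need data missing completely at random, and unequal attrition is not in itself a bias.* Both are correct. A reader might infer from the one-sided case management that the primary contrast must be biased. The check does not support this: loss may depend on covariates in the model, arm is one of them, and the arm-only runs show no bias.

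*A longitudinal GEE recovers much of the loss.* This stands for loss driven by earlier condom use. In a large simulation with 12/28 attrition, AR-1 GEE gave 10.0 and 10.1 against true effects of 10.1 and 10.2 when loss followed the 6-month outcome, and 9.9 when it followed baseline condom use. That data model favours AR-1. The recovery does not extend to a baseline trait outside the model that drives loss at both visits, nor to unseen 12-month condom use, where the same simulation gave 7.0 to 7.5. So imputation or weighting does add something, although neither repairs the last case.

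*Differential attrition is inferred.* This also stands. The common tracing, incentives and transport argue against a large difference between arms.

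**Conclusion.** The concern holds in limited form. The Analysis section presents unweighted available-case GEE as sufficient for intention to treat. With 20% planned attrition, that is true only if loss is unrelated to the outcome given the model covariates and, approximately, earlier outcomes when the working correlation is right. The one-sided monthly contact makes a breach plausible; the document does not show that one will occur.

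The size is roughly 0.6 to 4 points against a target of 10 to 15. It rests on assumed splits of 12/28 or 16/24, assumed links between loss and condom use, and simulations that simplify the design. A reader might take the worked example (10 points estimated as 6.8) as an established bias of 3.2 points. It is not: it is a 12-month calculation among women seen, on assumed inputs, and the planned model uses earlier visits as well. The direction is not settled either. Understatement is the likelier case if controls lose more high-risk women.

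**What to change.** In the Analysis section:

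1. Stop presenting available-case GEE as sufficient for intention to treat. State the missingness assumption under which it is valid.
2. Report attrition by arm at 6 and 12 months.
3. Analyse the primary outcome with multiple imputation by arm, or with inverse-probability-weighted GEE. Use zone, baseline condom use, HIV status, sex work, alcohol and drug use, and the 6-month outcome. Report the result beside the available-case GEE.
4. Add a delta-adjusted sensitivity analysis for loss that depends on unobserved condom use, since step 3 does not repair that.

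The cost is more analysis work and possibly slightly wider intervals. The predictors come from data already collected, so no new data are needed.

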#### Outcome measures

The primary outcome is self-reported male or female condom use during the participant’s most recent episode of vaginal or anal intercourse. Other outcomes include frequency of condom use, frequency and quantity of alcohol use, urine drug screen results for illicit substance use, and frequency of violent victimization (physical or sexual). Additional outcomes for women living with HIV include receiving HIV treatment, ART adherence, and CD4 counts. Analyses for HIV-RNA viral load on stored dried blood spots at follow-up may occur at a later date.

Alcohol use is measured biologically with a breathalyzer test and through self-report. A biological urine drug screening test determines recent use of a panel of substances, including cannabis/marijuana, opioids, cocaine, methamphetamine, and Mandrax (methaqualone). Victimization includes self-report of being beaten, attacked with a weapon, or forced to have sex during the previous 90 days. We assess if women living with HIV received treatment and took ART both biologically and by self-report. Self-report for ART refers to being prescribed ART, taking ART if prescribed, and missing any doses in the past 30 days. We also examine measures of adherence included in the U.S. National Institute on Drug Abuse’s harmonization initiative [30]. To help interpret these data, we also collect self-reports of barriers to ART use.

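### The Analysis section assigns a logit link to count outcomes, which is wrong for any non-primary outcome analysed as a raw count; the binary primary outcome is unaffected.

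*Protocol article*

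**What the plan says.** The Analysis section sets the model for the repeated outcomes at baseline, 6 and 12 months: "our primary analytic strategy will apply a generalized estimating equation (GEE) modeling approach". It then allocates links by type of outcome. Binary and count outcomes share one link: "For outcomes with binomial or count distributions, the logit link will be specified to obtain effect estimates". The other rule reads "For continuously distributed outcomes, an identity link function will be specified". The article names no log link, no Poisson or negative binomial variance, no denominator for counts and no rule for dichotomising them.

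Under Outcome measures there is a single primary outcome: "The primary outcome is self-reported male or female condom use during the participant", asked about the most recent vaginal or anal intercourse. The other outcomes there include "frequency of condom use, frequency and quantity of alcohol use" and the frequency of violent victimization. The Sample size and power section gives as examples of behavioural outcomes "reductions in AOD use, number of instances of unprotected sex".

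**The concern.** The sentence lists counts separately from binomial outcomes, so on its plain reading the logit applies to counts as such. A count of unprotected acts has no upper bound at 1, and a logit model cannot describe its mean.

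The plan's second aim is to reduce risk behaviours among all women, and some of the outcomes serving that aim may be counts. If the stated model fails on them, someone must decide after unblinded data are in hand whether to change the link, introduce a denominator or reduce the count to any/none. Each choice answers a different question and can give a different result. Any/none in particular asks whether an event happened at all, which is a weak question when most women have at least one.

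**Working it through.** There is no stated figure to reproduce, because the point is about a link function.

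**1. Algebra.** With a logit link, log[μ/(1−μ)] = η, so μ = 1/(1+e^(−η)). This lies strictly between 0 and 1 for every η. No coefficients can give a mean of 1 or more.

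**2. Simulated check.** Poisson counts for 480 women in 14 clusters were fitted by GEE in statsmodels, with an independence working correlation. The means are assumptions; the article gives none.

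| True means (control, intervention) | Binomial family, logit link | Poisson family, log link |
|---|---|---|
| 0.3, 0.2 | converged; fitted 0.262, 0.246 | converged; fitted 0.262, 0.246 |
| 3, 2 | overflow, no convergence | converged; fitted 3.08, 1.83 |
| 6, 5 | overflow, no convergence | converged; fitted 5.96, 4.88 |

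The software rejected a Poisson family with a logit link as invalid. In the low-mean row both models return the same fitted means but different effects. The log-link coefficient −0.0656 gives a rate ratio of e^(−0.0656) = 0.94. The logit coefficient −0.0879 gives e^(−0.0879) = 0.92. The latter is a ratio of μ/(1−μ) with μ a mean count, so it is neither a rate ratio nor the odds ratio for having any event.

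**3. Are means of 1 or more plausible?** The Study population section requires unprotected vaginal sex in the past 6 months and at least weekly use of alcohol or another drug over 90 days. If unprotected acts are counted over 6 months, every woman has at least one at entry. A woman who qualifies through alcohol has about 90/7 ≈ 13 drinking occasions in 90 days. Baseline is one of the modelled time points. This supports means of 1 or more for some outcomes at baseline; it says nothing about victimization or about follow-up.

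**4. Cost of falling back on any/none.** From the article: about 480 women at 12 months, two-sided 0.05, and a 10% to 15% difference, read here as a relative reduction. Assumed: an equal split (240 per arm), control mean 8, negative binomial dispersion k = 1, no clustering.

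- Count: SE = √{[(1/μ₀ + 1/k) + (1/μ₁ + 1/k)]/240}, z = |ln(μ₁/μ₀)|/SE.
- Any/none: P(0) = [k/(k+μ)]^k = 1/(1+μ), two-proportion z with unpooled SE.
- Power = Φ(z − 1.96) + Φ(−z − 1.96).

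15% reduction, 8 to 6.8:
- Count: SE = √[(0.125 + 1 + 0.147 + 1)/240] = 0.0973; z = 0.1625/0.0973 = 1.67; power 39%.
- Any/none: 1 − 1/9 = 88.9% vs 1 − 1/7.8 = 87.2%; difference 0.0171, SE 0.0296, z = 0.58; power 9%.

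10% reduction, 8 to 7.2:
- Count: SE = √[(0.125 + 1 + 0.139 + 1)/240] = 0.0971; z = 0.1054/0.0971 = 1.085; power 19%.
- Any/none: 88.9% vs 1 − 1/8.2 = 87.8%; difference 0.0108, SE 0.0293, z = 0.37; power 7%.

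**5. Low means.** For Poisson counts with means 0.3 vs 0.2, SE = √[(1/0.3 + 1/0.2)/240] = 0.186 and z = 0.4055/0.186 = 2.18, so power is 59% as a count. Any/none is 1 − e^(−0.3) = 25.9% vs 1 − e^(−0.2) = 18.1%, with power 54%. Little is lost.

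**The case against.** The strongest reply is that the slip reaches less of the trial than it seems to.

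- **The primary outcome.** A reader might infer that the main comparison is invalid, the more so because the Analysis section speaks of primary outcomes in the plural. Outcome measures names only one, it is binary, and the logit is correct for it. Drug-screen results and receipt of HIV treatment are naturally binary too, and CD4 cell count is naturally handled as continuous under the identity link. This stands.
- **Which outcomes are counts.** A reader might infer that several listed outcomes are unbounded counts. The only explicit count is the number of unprotected acts, and it appears as an example in the power section. "frequency and quantity of alcohol use" has no stated scale; it could be days in a fixed period, ordinal or continuous. Condom-use frequency could be a proportion, and victimization could be yes/no. An article may leave scales to the full protocol. This stands, and it limits the point to whichever outcomes are analysed as raw counts.
- **Unfittable or yes/no.** These are not the only two options. Protected acts out of all acts, or days out of a fixed period, can be fitted as events/trials with a logit. This stands, although such an outcome is binomial, the article lists counts separately, and it gives no denominator.
- **Size.** A larger effect makes a more striking contrast: with the same formulas, a 25% reduction (8 to 6) gives 84% vs 18%. Nothing in the article supports 25%. At its own 10% to 15%, power is low either way under these assumptions. The article gives no intracluster correlation, so no design effect is applied; clustering would lower all the figures.

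None of this repairs the sentence. It positively fixes a link for counts, nothing else in the article corrects it, and it is therefore not a detail left to another document.

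**Conclusion.** The sentence is wrong as written for any non-primary outcome analysed as a raw count. That the logit cannot represent a mean of 1 or more is algebra and rests on no assumption. Which outcomes are affected depends on scales that the article does not give: certainly the number of unprotected acts if it is analysed as a count, and any alcohol-use, condom-use or victimization frequency recorded as one.

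The main consequence is an unplanned choice of link, denominator or cut-point after the data are seen. If that choice is any/none, the illustration gives 7% to 9% power against 19% to 39% for the count. Those figures depend on the assumed mean, dispersion, equal split and absence of clustering, and on reading the 10% to 15% as relative. The direction is firm when the mean is well above 1, and the loss is small at low means. The documents do not support extending the point to the primary outcome.

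**What to change.** Amend the sentence on links in the Analysis section:

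- Restrict the logit link to binary outcomes and to outcomes with a known denominator, modelled as events/trials (for example protected acts out of all acts, or days out of a fixed period).
- For unbounded counts, specify a log link with negative binomial or Poisson variance and robust standard errors in the GEE, and report rate ratios.
- State for each listed outcome which class it falls in, before follow-up data are examined by arm.

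The identity link for continuous outcomes can stay. The cost is a revised sentence and a short classification of outcomes. No data collection changes, the primary analysis is untouched, and the extra analysis work is negligible.
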